#### Statistical methods

Firstly, an analysis of the comparability of the groups will be performed using the Student-s T-test or Mann-Withney's Test and test of Chi^2 ^or Fischer's exact test. Subsequently, the effects found in the patients of the experimental group and the control group will be described using the difference of averages or ranges and risk ratios. These descriptions will be accompanied by their respective confidence intervals and hypothesis tests (as the ones mentioned above). When the result of the first analysis makes it necessary, possible confusion or the presence of interaction will be controlled using linear and logistic regression models.

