### Sample Size

For the calculation of the sample size we make the following assumptions:

• The effect of the standard treatment on the control group will cause an average limb volume reduction of 5%.

• The effect of the treatment on the experimental group will cause an average limb volume reduction of 25%

• We also assume that the standard deviation will be similar in both groups and near to 25%. With this information and with an alpha risk of 0.05 and a power of 0.80, the calculation of the sample size is 20 patients in each group. Considering a 30% dropout rate in each group, the corrected sample size is 58 patients randomized in two groups of 29 patients each.

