### Statistical analysis

All patients included in the study will be analyzed and all the analyses will be performed in the "intention to treat" population, except those related to the withdrawal of treatment, which will be performed in the per-protocol population.

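### Covariate adjustment is made to depend on between-group comparability tests, when baseline volume should be a pre-specified covariate in the primary model

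*Protocol article*

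**What the plan says.** The Statistical methods section of the protocol article sets out a sequence.

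- Step one: "Firstly, an analysis of the comparability of the groups will be performed using the Student-s T-test" or its rank-based counterpart, with chi-square or Fisher's test for categorical variables.
- Step two: treatment effects are reported as differences or risk ratios, with confidence intervals and the same two-sample tests.
- Step three, conditional on step one: "When the result of the first analysis makes it necessary, possible confusion or the presence of interaction will be controlled", by linear and logistic regression.

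The Efficacy analyses section adds no adjusted comparison. The word baseline does not appear in the sequence, but a comparability check that comes before the effect analysis and decides whether to control confounding is most naturally a check of baseline characteristics.

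The Primary Outcome section expresses volume reduction as a percentage and defines a good response relative to baseline. Under Interventions and distribution of tasks, both arms of each patient are measured at the selection visit, so baseline excess volume is already collected.

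**The concern.** After sound randomisation, any baseline difference between groups is due to chance, so a significance test of it answers no useful question. It is also a poor guide to when adjustment matters. That depends on how strongly the covariate predicts outcome as well as on the size of the imbalance, and in a trial of 58 patients a sizeable imbalance can be non-significant.

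The rule therefore does two things. It leaves unflagged imbalance in the estimate, and it gives up the precision that a prognostic covariate brings even when the groups are balanced. It also means that whether to adjust, and for what, is settled after the data are seen. At stake are the efficiency of a small trial and the credibility of its estimate for the particular randomisation obtained.

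**Working it through.** **Inputs.** From the Sample Size section: mean reductions of 5% and 25% (difference 20 points), SD 25, 30% dropout, and "with an alpha risk of 0.05 and a power of 0.80". Sidedness is not stated. Assumed, because the document gives no figure: a within-group correlation r between baseline volume and percentage reduction of 0, 0.3, 0.5 or 0.7, and a trigger of p<0.05.

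**1. The plan's own figure.** n per group = 2 × [SD × (z_alpha + z_power) / difference]².
- One-sided 0.05: 2 × [25 × (1.645 + 0.842) / 20]² = 19.3, so 20. Then 20 / 0.7 = 28.6, so 29 per group and 58 in total. This reproduces the plan.
- Two-sided 0.05: 2 × [25 × (1.960 + 0.842) / 20]² = 24.5, so 25. This does not.

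**2. Imbalance the test does not flag.** Largest non-significant difference, in SD units = t(0.975, 2n−2) × √(2/n).
- n = 29: 2.003 × 0.263 = 0.53 SD.
- n = 20: 2.024 × 0.316 = 0.64 SD.

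**3. Shift in the unadjusted estimate at that limit.** Shift = r × imbalance × 25 points.

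| r | 29 per arm | 20 per arm |
|---|---|---|
| 0.3 | 3.9 | 4.8 |
| 0.5 | 6.6 | 8.0 |
| 0.7 | 9.2 | 11.2 |

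The planned effect is 20 points. These are upper limits, and the shift can go in either direction.

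**4. False alarms.** With k independent baseline variables, the chance of at least one p<0.05 is 1 − 0.95^k: 23% for k = 5 and 40% for k = 10, under sound randomisation.

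**5. Required size with adjustment.** ANCOVA multiplies the residual variance by 1 − r². Two-sided, 24.53 × (1 − r²) gives 22.3, 18.4 and 12.5 at r = 0.3, 0.5 and 0.7. That is 23, 19 and 13 per group, against 25 unadjusted.

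**6. Simulated power.** 40,000 trials per setting, normal data, one baseline covariate, effect 20/25 = 0.8 SD, two-sided 0.05. The stated rule is taken as ANCOVA if the baseline test has p<0.05, and otherwise the unadjusted t-test.

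| n per arm | r | Unadjusted | Stated rule | Pre-specified ANCOVA |
|---|---|---|---|---|
| 20 | 0 | 0.70 | 0.70 | 0.69 |
| 20 | 0.3 | 0.70 | 0.70 | 0.72 |
| 20 | 0.5 | 0.69 | 0.70 | 0.80 |
| 20 | 0.7 | 0.69 | 0.71 | 0.93 |
| 29 | 0.3 | 0.85 | 0.85 | 0.87 |
| 29 | 0.5 | 0.85 | 0.86 | 0.93 |
| 29 | 0.7 | 0.85 | 0.87 | 0.99 |

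Conditional adjustment recovers little of the available gain.

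**7. Simulated type I error.**
- Over all randomisations, the stated rule gives about 4.7–4.8% / 4.3–4.4% / 3.8% at r = 0.3 / 0.5 / 0.7, and about 5% at r = 0. It is not inflated.
- In trials where the baseline test falls at p between 0.05 and 0.20, which is 0.20 − 0.05 = 15% of randomisations, the unadjusted test has a conditional error of about 6% / 9% / 12%. ANCOVA stays at about 5%.

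**The case against.** The strongest reply is that an unadjusted comparison is valid under randomisation, that flagged imbalance would be adjusted, and that the size of any gain rests on a correlation the document does not give. All of this stands. A correlation with raw follow-up volume would not carry over to percentage change, and at r = 0.3 the gain with 20 per arm is only about 2 points. The limits in step 3 are also rarely approached: with 29 per arm, an imbalance of at least 0.5 SD has p = 0.062, so one between 0.5 SD and the cut-off arises in about 6.2% − 5.0% = 1.2% of randomisations. None of this favours keeping the trigger, since the downside of pre-specified adjustment is about 1 point of power when r = 0.

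A reader might infer more than the document supports:

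- **That baseline volume is discarded.** It is not, because the outcome is a percentage reduction from baseline. It is absent only as a covariate.
- **That chance imbalance goes uncorrected.** This is true only of imbalance the tests do not flag.
- **That the two-stage rule inflates the false-positive rate.** Overall it does not; the rise is conditional.
- **That the analysis will be restricted to completers.** The Statistical analysis section says "All patients included in the study will be analyzed" and specifies intention to treat. How dropouts are handled is detail an article may leave to the full plan.
- **That the trial is shown to be underpowered.** That depends on the unstated sidedness and is a separate matter. One-sided, 20 per arm gives power of about 0.80.
- **That a repeated-measures model over all visits is the remedy.** Under Treatment groups and the task list, poor responders change treatment at about week 12, so later volumes would mix treatments. The Primary Outcome section also names no single primary visit.

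**Conclusion.** The point holds as one of efficiency and conditional bias. The protocol states a poor rule; it does not merely leave a detail open. If the trigger is p<0.05, baseline imbalances up to about 0.53 SD (29 per arm) or 0.64 SD (20 per arm) remain in the estimate, and the choice of model follows the data. Relative to the stated rule, pre-specified ANCOVA with 20 completers per arm would raise two-sided power by about 2, 10 and 22 points at r = 0.3, 0.5 and 0.7. The rule itself recovers at most about 2 points over the unadjusted test.

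The existence of the problem does not depend on these assumptions, but its size does: the correlation, the p<0.05 threshold, two-sided testing, normal data and a single covariate. The change is worth making, but the trial is not invalid without it.

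**What to change.** In Statistical methods, delete the sentence that makes regression depend on the comparability analysis, and report baseline characteristics descriptively without tests. State that the primary analysis is a linear model (ANCOVA) of percentage volume reduction on treatment group, with baseline excess volume as covariate whatever the observed balance, giving the adjusted difference and its confidence interval. Keep the unadjusted two-sample comparison as a supportive analysis.

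This is a change of wording only. The covariate is already measured at the selection visit, so no visits, patients or data are added. The statistical price is about 1 point of power if baseline volume turns out to be unrelated to outcome.

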### Subjects of study

Caucasian women with lymphoedema who have undergone a prior mastectomy, tumorectomy or quadrantectomy and axillary lymphadenectomy. A sample size of 58 patients randomized in 1:1 ratio (29 per group) will be required.

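### Handling of interaction in the efficacy regressions is triggered by baseline comparability tests, which carry no information on effect modification, and the text does not say that the average MLD effect remains the trial result

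*Protocol article*

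**What the plan says.** The Statistical methods section of the protocol article sets out three steps.

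1. The groups are compared with t or Mann-Whitney tests and chi-square or Fisher tests.
2. The effects in the two groups are described by differences of averages or ranges and by risk ratios, with confidence intervals and tests. This step is unconditional.
3. If the first analysis makes it necessary, "possible confusion or the presence of interaction will be controlled using linear and logistic regression models".

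In that order, the first analysis is the comparability testing. No covariate or effect modifier is named. The section does not say how a model with an interaction would be summarised, or how its result ranks against the unadjusted difference.

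The Efficacy analyses section again lists mean or median differences, risk ratios and the number needed to treat, with confidence intervals. It mentions no regression.

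The Sample Size section rests on the average difference between arms: "The effect of the standard treatment on the control group will cause an average limb volume reduction of 5" percent, against "The effect of the treatment on the experimental group will cause an average limb volume reduction of 25" percent, with the assumption that "the standard deviation will be similar in both groups and near to 25" percent.

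**The concern.** Two things in the stated rule are wrong.

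- **The trigger.** A comparability test asks whether a covariate is distributed alike in the two arms. Effect modification asks whether the MLD effect on the outcome differs across levels of that covariate. The first question has no bearing on the second, and in a randomised trial any imbalance is due to chance.
- **The aim.** Confounding is a distortion that adjustment can remove. Interaction is a feature of the treatment effect, so the task is to estimate and describe it.

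At stake is what the treatment coefficient means. In a linear model with main effects only, it estimates the average difference. Once a treatment-by-covariate term is added without centring, it becomes the effect at the reference level, or at covariate value zero. For baseline excess volume, zero lies outside the trial, because the inclusion criteria require a difference of at least 200 ml. An analyst who follows the rule and reads that coefficient as the MLD effect would report a different quantity, estimated less precisely, and would do so because of a chance imbalance.

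**Working it through.** **Inputs from the Sample Size section.** Difference 25 − 5 = 20 points; SD 25; "with an alpha risk of 0.05 and a power of 0.80"; 20 evaluable per arm; 29 randomised per arm after a 30% dropout allowance.

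**Assumption, not in the document.** One binary covariate with half the patients at each level; shares of 30% and 20% for the reference level are shown as a range.

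**The plan's own figure.** n per arm = 2 × SD² × (z_α + z_β)² / difference².
- One-sided: 2 × 625 × (1.645 + 0.842)² / 400 = 19.3, so 20. This matches "the calculation of the sample size is 20 patients in each group".
- Two-sided: 2 × 625 × (1.960 + 0.842)² / 400 = 24.5, so 25. This does not match.
- Dropout: 20 / 0.7 = 28.6, so 29 per arm and 58 in all, as stated.

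The stated 20 therefore reproduces only as a one-sided calculation. That is a separate matter. It explains why two-sided power at 20 per arm starts below 80% in the figures below.

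**Does the trigger detect interaction?** Simulation of 8,000 trials per setting: 29 per arm, 50% binary covariate, average effect 20 points, SD 25, chi-square baseline test at the 5% level.

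| True interaction (points) | Baseline test significant | Interaction significant, all trials | Interaction significant, given the trigger |
|---|---|---|---|
| 0 | 4.9% | 5.1% | 5.1% |
| 20 | 4.2% | 31.7% | 29.2% |
| 40 | 4.8% | 83.5% | 82.3% |

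The baseline test fires at about its nominal rate whatever the interaction, and its firing leaves the chance of finding an interaction essentially unchanged.

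**Precision of the uncentred coefficient.** SE of the average effect = SD × √(2/n). SE of the effect at a reference level with share s = SD × √(2/(n·s)), so the ratio is 1/√s, which is √2 = 1.41 at s = 0.5. Power is two-sided at 0.05 from the noncentral t distribution, with 2n − 2 degrees of freedom without the covariate and 2n − 4 with the covariate and its interaction.

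| Per arm | SE, average effect | Power | SE, uncentred, s = 0.5 | Power |
|---|---|---|---|---|
| 29 | 25√(2/29) = 6.57 | 85% | 6.57 × 1.41 = 9.28 | 56% |
| 20 | 25√(2/20) = 7.91 | 69% | 7.91 × 1.41 = 11.18 | 41% |

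With a reference level of 30% or 20% of patients, the ratio is 1.83 or 2.24. Power is then 37% or 27% at 29 per arm, and 27% or 20% at 20 per arm.

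**What the coefficient estimates.** With a true interaction of 20 points and an average effect of 20, the effect at the reference level is 20 − 0.5 × 20 = 10. In the simulation at 29 per arm the uncentred coefficient averaged 9.9 and the centred one 20.0.

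**The same model, centred.** With no true interaction, the empirical SD of the estimate was 6.65, against 6.59 for the simple mean difference, at 29 per arm (power 84%). At 20 per arm it was 7.98 against 7.85 (power 68%).

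**The case against.** The strongest reply is that the average effect is never abandoned. Statistical methods commits without condition to the difference of averages with its interval and test, Efficacy analyses repeats the same measures, and nothing says that a regression supersedes them. The wording also refers to interaction being present, which suggests a second judgement after the imbalance; the baseline test alone fires in only about 4% to 5% of trials per covariate. Coding and summary of a model are details that a full protocol or analysis plan may hold.

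Most of this stands, and it rules out a stronger reading. A reader might infer that an interaction term necessarily replaces the average MLD effect with an imprecise subgroup effect. The document does not say so, and it is not true of interaction models in general, as the centred results show.

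A reader might also want to put a larger figure on the loss by taking uncentred excess volume as the covariate. The document gives no mean or SD for it and does not name it as a covariate. The inflation factor is √(1 + (mean/SD)²). For an assumed mean of 350 to 600 ml and SD of 150 to 300 ml, it runs from 1.54 (350/300) to 4.12 (600/150), and power at 20 per arm from 36% down to 9%. That range is too wide and too dependent on assumption to carry the point.

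The reply does not rescue the rule itself. The trigger is uninformative however the model is coded, and interaction remains the wrong target for control. This is a fault in what the article states, not detail left to another document.

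**Conclusion.** The point holds as a fault in the stated rule, with a consequence that is possible but not certain. The trigger cannot reveal effect modification, and the text gives no ranking between the unadjusted difference and a regression result. It therefore leaves room for the trial to be summarised by a coefficient that is not the average effect it was sized for.

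The quantified loss (power of 56% instead of 85% with all 29 per arm, 41% instead of 69% with 20 per arm) requires all of the following: the term is added, the covariate is binary and evenly split, it is left uncentred, and the bare coefficient is reported as the result. If the covariate is centred, or the subgroup effects are averaged, the loss is negligible. The figures apply to the linear model for percentage volume reduction and take the planning difference and SD as true. The case for changing the sentence rests mainly on the faulty logic of the rule.

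**What to change.** In Statistical methods, delete both the reference to interaction and the dependence on the comparability tests. State instead that:

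- the adjusted efficacy model contains treatment and pre-named baseline covariates (for example baseline excess volume) as main effects, whatever the baseline comparison shows;
- the average MLD effect is the primary estimate;
- any treatment-by-covariate interaction is pre-named, fitted with the covariate centred, and reported as exploratory beside the average effect.

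The cost is a short rewrite and a decision on covariates before the data are seen. The sample size and the conduct of the trial do not change. The downside is that real effect modification would be reported only as exploratory. Little is given up, because the trial is weak for it anyway: with an evenly split covariate the interaction has twice the SE of the average effect (2 × 6.57 = 13.13 at 29 per arm), and power for a 20-point interaction is about 33% by the normal approximation.

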#### Efficacy analyses

The analyses of the efficacy will be carried out using common measures such as mean and/or median ratio differences for the quantitative variables and risk ratios (relative risk) and NNT for the quantitative variables.

In all cases, the corresponding confidence intervals will be calculated.

##### Safety Analyses

Side effects, withdrawal and/or complication rates will be studied in the same way as those described for the quantification of the efficacy in the case of qualitative variables. In all case analyses, the confidence intervals will be also calculated.

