### Treatment groups

#### Group A or Control Group

Ambulatory treatment is performed for one month. Specific exercises and prevention measures are taught. In the first four weeks, multilayer bandage is applied daily. Bandaging consists of a first layer of cotton (Velband) followed by protection at the points of support and a bandage of low elasticity (Comprilan) of different widths (six centimeters for the area of the hand and eight centimeters for the rest of the extremity).

The tailor-made sleeve for lymphoedema with a gauntlet without protection at the edges and with extension to the shoulder is applied for the first four weeks of treatment. The sleeve is used all day, and at night interruption is allowed. Later on, the patient will continue domiciliary treatment, performing specific exercises for 30 minutes twice a day without experiencing fatigue, and wearing the lymphoedema sleeve for at least 12 hours.

If after three months of treatment a satisfactory response is not achieved, an ambulatory treatment will be re-established for one month, and this time the experimental treatment (group B) will be used.

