#### - Group B. Experimental group

Ambulatory treatment is carried out for one month. Specific exercises and prevention measures are taught. In the first four weeks, MLD is applied followed by a daily multilayer bandage. The bandage consists of a first layer of cotton (Velband) followed by protection at the points of support and a bandage of low elasticity (Comprilan) of different widths (six centimeters for the area of the hand and eight centimeters for the rest of the extremity). The tailor-made sleeve for lymphoedema with a gauntlet without protection at the edges and with extension to the shoulder is applied for the first four weeks of treatment. The sleeve is used all day, and at night interruption is allowed. Later on, the patient will continue domiciliary treatment, performing specific exercises for 30 minutes twice a day without experiencing fatigue, and wearing the lymphoedema sleeve for at least 12 hours.

If after three months of treatment a satisfactory response is not achieved, an ambulatory treatment will be re-established for one month, and this time the treatment corresponding to group A or control group will be applied.

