### Interventions and distribution of tasks

The rehabilitation physician's functions include:

1. Selection call: the physician determines whether the patient meets inclusion criteria and if so, she is randomized into a treatment group. He/she carries out a complete medical history (history and complete physical exam, taking measurements of both upper extremities for the calculation of lymphoedema volume). He/she explains and provides the informed consent and collects the signed copy. He/she gives the quality of life questionnaire to the patient, who will complete it before starting the outpatient treatment.

2. Week 2 of treatment: Examine the patient. Take measurements of the upper extremities. Rule out the existence of treatment-related side effects. Make the request for a lymphoedema garment. Collect the quality of life questionnaires.

3. Week 5 of treatment: Examine the patient. Take measurements of the upper extremities. Rule out the existence of treatment-related side effects. Check the sleeve. Give a compliance diary to the patient.

4. Week 12 of treatment: To examine Explore the patient. Ask about possible complications that may lead to withdrawal from the study. Take measurements of both upper extremities. If the response to the treatment is good, the patient will be encouraged to continue complying with treatment. The patient's diary is reviewed. A second quality of life questionnaire is provided. The treatment is continued at home. If the response to the treatment is poor, the patient is included again in an outpatient treatment for a month so that if the patient has previously received TH now he/she would be treated with TH + DL and if he/she has been previously treated with TH + DL now she would be treated with DL. The patient is examined at week 16. Measurements of the upper extremities are taken. The presence of treatment-related side effects is ruled out.

5. Week 18 of treatment: the patient is examined. Measurements of the upper extremities are taken. The presence of treatment-related side effects is ruled out. The sleeve is reviewed. A second quality of life questionnaire is delivered.

6. Final call: Week 24 of treatment: the patient is examined. The patient is asked about possible complications that may lead to withdrawal from the study. Measures are taken in both upper limbs. The sleeve is reviewed.

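### Side effects are analysed by randomised arm with no cut-off at the planned week-12 switch, so MLD side effects in switched controls can be counted against the control arm

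*Protocol article*

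**What the plan says.** All references are to the Protocol article.

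- **Population.** Statistical analysis: "all the analyses will be performed in the" intention-to-treat population. The only exception is analyses related to withdrawal of treatment, which use the per-protocol population. Side effects and complications are outside that exception.
- **Method.** Safety Analyses: "Side effects, withdrawal and/or complication rates will be studied in the same way as those described for the quantification of the efficacy". The sentence goes on to limit this to the approach for qualitative variables, that is, risk ratios, NNT and confidence intervals. It sets no time window and no rule for attributing an event to the treatment received.
- **Switch from control.** Group A or Control Group: after three months without a satisfactory response, "an ambulatory treatment will be re-established for one month, and this time the experimental treatment (group B) will be used".
- **Switch from MLD.** Group B: for the same trigger, "this time the treatment corresponding to group A or control group will be applied". The week-12 item of Interventions and distribution of tasks describes a different second treatment for these patients.
- **Checks.** Interventions and distribution of tasks has side effects checked at weeks 2 and 5, and complications asked about at week 12. Directly after the poor-response instruction it adds: "The patient is examined at week 16", with a further side-effect check. Week 18 is a separate item with a side-effect check and no restriction to re-treated patients. Week 24 asks about complications.

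**The concern.** Up to week 12 the arms differ by MLD, as randomised. After week 12 a planned, response-driven group of controls receives MLD. A side effect that MLD causes in one of them is, under the stated population rule, an event in the control arm. The control rate rises and the apparent excess on MLD shrinks.

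For harms, a pull towards no difference is the unsafe direction, because it can make MLD look as if it adds little. The Discussion links the results to decisions on providing more staff trained in the technique, so the side-effect comparison may be used.

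There is also a smaller problem of unequal checking. The week-16 check reads as applying to re-treated patients only, and these are expected to be more frequent among controls. The week-18 check of all patients limits this but does not remove it.

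**Working it through.** **1. What can be reproduced.** The article states no side-effect rate and no expected share of switchers. Its dropout correction does reproduce: 20 / (1 − 0.30) = 28.6, rounded up to 29 per group. The same 30% is used below.

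**2. Share expected to switch.** Inputs: mean reductions of 5% (control) and 25% (MLD) and SD 25% from Sample Size; good response of at least 20% from Primary Outcome. Three assumptions are needed: responses are normal, a satisfactory response means a good one, and the limb-volume figures in Sample Size apply to the lymphoedema-volume threshold in Primary Outcome.

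- Control: Φ((20 − 5)/25) = Φ(0.6) = 0.726, or 21.0 of 29.
- MLD: Φ((20 − 25)/25) = Φ(−0.2) = 0.421, or 12.2 of 29.
- If all 30% dropout precedes week 12, randomised controls who switch: 0.70 × 0.726 = 0.508, or 14.7 of 29.
- Sensitivity: for SD from 15% to 30%, the control share among those reaching week 12 runs from 84% to 69%.

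**3. Effect on the side-effect comparison.** All event rates here are assumed. Let b be the risk in a treatment month and a the risk added by MLD. The home-treatment period is taken to add no risk. A re-treated MLD patient is given a second month at risk b, following the Group B section.

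- To week 12: control b; MLD 1 − (1 − b)(1 − a).
- To week 24, control: 1 − (1 − b)(1 − 0.726 × [1 − (1 − b)(1 − a)]).
- To week 24, MLD: 1 − (1 − b)(1 − a)(1 − 0.421b).
- With early dropout, 0.726 and 0.421 are each multiplied by 0.70.

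With b = 5% and a = 10%:

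| Comparison by randomised arm | MLD | Control | Risk ratio | Difference (points) |
|---|---|---|---|---|
| To week 12 | 14.5% | 5.0% | 2.9 | 9.5 |
| To week 24, no dropout | 16.3% | 15.0% | 1.09 | 1.3 |
| To week 24, 30% dropout before week 12 | 15.8% | 12.0% | 1.31 | 3.8 |
| To week 24, no dropout, no base risk in second month | 14.5% | 11.9% | 1.22 | 2.6 |

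In the last row the control risk is 1 − 0.95 × (1 − 0.726 × 0.10) = 0.119.

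**4. Range.** Over b from 2% to 10% and a from 10% to 20%:

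| | Smallest (b = 10%, a = 10%) | Largest (b = 2%, a = 20%) |
|---|---|---|
| Difference to week 12 | 9.0 points | 19.6 points |
| To week 24, no dropout | 0.0 points | 4.9 points |
| To week 24, early dropout | 2.7 points | 9.3 points |

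The difference shrinks in every cell.

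**5. Dependence on the second treatment in the MLD arm.** The Group B section and the week-12 item disagree on what these patients receive. If their second month carried the 10% MLD risk instead of the 5% base risk, the first example becomes 1 − 0.95 × 0.90 × (1 − 0.421 × 0.10) = 18.1% against 15.0%, a risk ratio of 1.21. This is still far below 2.9.

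**The case against.** **The window is not stated.** A reader might infer that the plan compares side effects over the whole six months. It does not say so. Studying them in the same way as efficacy refers to the effect measures, and efficacy is assessed at one, three and six months, so reporting by visit would fit the text. A fuller protocol or SAP could set a window. This stands, and the point is therefore conditional: it applies to any by-arm comparison that includes the period after the switch. It does not dissolve the point, because the article fixes the population for all analyses, names a single exception, and collects side effects after the switch.

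**Most controls.** A reader might infer that most randomised controls will receive MLD. The documents do not state this. The 73% applies to those who reach week 12; with early dropout it is about half of those randomised.

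**All safety analyses.** A reader might take the quoted safety sentence to put everything under intention to treat. Analyses related to withdrawal of treatment are per-protocol, so the point covers side effects and complications only.

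**Six months by arm is legitimate.** It summarises a policy of starting with or without MLD, response-driven switch included. That is a fair reason to keep it, but it does not isolate what MLD adds.

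**Little practical consequence.** Safety is not among the listed outcomes, and precision is low in either window. For 14.5% against 5.0% with 29 per arm, the standard error is √(0.145 × 0.855/29 + 0.05 × 0.95/29) = 0.077, so power at two-sided 5% is about Φ(0.095/0.077 − 1.96), roughly 23%. The trial could not establish absence of added harm either way. Low precision is still no reason to add a bias of known direction.

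**Conclusion.** The point holds in conditional form. As written, the population rule attributes to the control arm any MLD side effect that arises in a control after the planned switch, and nothing in the article separates the two periods.

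The share who switch rests on the plan's own figures plus the three assumptions in step 2. About 42% of MLD patients who reach week 12 would also be re-treated. The size of the dilution rests on assumed event rates. In the example the risk ratio falls from 2.9 to between 1.09 and 1.31, depending on dropout and on whether the second month carries base risk. The direction is the same across the range examined; the exact values should not be read as predictions.

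The documents do not support the stronger conclusion that the trial will report MLD as free of added side effects. They fix neither the safety window nor any event rate.

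**What to change.** - Make the main comparison of side effects and complications by randomised arm, from start of treatment to the week-12 visit and before any re-treatment, with risk ratio and confidence interval.
- Report the six-month by-arm result as supplementary.
- Tabulate later events by the treatment being received at onset. Show week-16 findings separately, because that check reads as covering re-treated patients only.
- Leave the analyses related to withdrawal of treatment as stated.
- Reconcile the Group B section with the week-12 item of Interventions and distribution of tasks on what switched MLD patients receive. Until that is done, their later events cannot be attributed.

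The cost is about one sentence in Safety Analyses and one extra table, with no change to visits or treatment. The downside is that the main comparison covers 12 weeks instead of 24, and its precision stays low with 29 per arm.
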